### Data collection and management

A checklist of the measures performed at each visit will be completed by the investigator and assessment visits will be scheduled as soon as the patient is discharged from hospital to promote participant retention and complete follow-up. Collected data will be implemented in the eCRF, data will be managed and processed by the clinical epidemiology unit at Robert Debré Hospital with independence from the sponsor. The biological samples collected for the determination of leptin and ghrelin will be stored in a biological collection, they will be kept in the Biochemistry and Hormonology Laboratory at Robert Debré hospital for the duration of the study. At the end of the research and after dosage, the samples will be destroyed. The AP-HP (Assistance Publique – Hôpitaux de Paris) is the sponsor and owner of the data and it may not be used or transmitted to a third party without its prior agreement. Audits may be conducted at any time by persons appointed by the sponsor and independent of the investigators. Its purpose is to ensure the quality of the research, the validity of its results and compliance with the law and regulations currently applicable. The persons responsible for the quality control of research involving the human person (article L.1121–3 of the French Public Health Code) will take all necessary precautions to ensure the confidentiality of information relating to the research, to the persons taking part in it and in particular to their identity and to the results obtained.

### Data analysis

#### Sample size

We calculated the sample size for a one-sided Student’s t test with a significance level of 2.5% and a power of 90% based on the clinically determined non-inferiority margin for a difference in BMI of 1 kg/m2, assuming a distribution of the BMI of 16,6 ± 1,35 kg/m^2^. This procedure led to a required sample size of 80 patients (40 per group). Assuming a dropout rate of 10% [8], we calculated a sample size of 88 patients. We aim to include 88 children with EOAN (44 per group).

#### Statistical analysis plan

The statistical analysis of the data will be performed using an intention-to-treat analysis, all patients allocated to the control group or experimental group will be analysed. The descriptive analysis for each group at each assessment time will be expressed as number (percentage) for categorical variables, and as mean (SD) or Median [IQR] according to their normal or non-normal distribution for quantitative variables. As described above, the primary outcome for non-inferiority analysis is based on the comparison of the BMI at 1 year after inclusion between the two groups with a two-sided 95% confidence interval. Experimental strategy will be considered as non-inferior if the confidence interval upper limit of the difference in BMI between the 2 groups is less than 1 kg/m^2^ (non-inferiority margin) with a 0.025 alpha risk. The comparative analysis between the 2 groups for the primary or secondary criteria will be carried out using the appropriate tests: Chi^2^ test or Fisher's exact test for qualitative variables; Student's t test or non-parametric Wilcoxon test for quantitative variables, according to their normal or non-normal distribution. To determine prognosis factors associated with positive response to stepped-care model of DP after short IP, a regression model will be used to search for factors associated with the effect of the intervention, integrating the MRS score as the explained variable, and the CGI score, the HAQ11 and motivation questionnaire scores, and the severity of the weight deficit as explanatory variables.

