### Procedure (Fig. 1)

**Fig. 1 Fig1:**
[figure not shown]
Study flowchart

At initial clinical assessment, eligible children and caregivers will be informed of the study and study protocol is fully explained by the investigator. After signature of the informed consent by the holder(s) of parental authority, target weight for weight normalisation will be calculated and participants will be randomised into one of the two trial arms. Weight normalisation is individualised and will be determined at inclusion and before randomisation to return to the previous BMI growth trajectory and is calculated by two different investigators [15–18].

Randomisation will be done by a randomisation list with the nQuery Advisor and nTerim 4.0 software implemented in the eCRF. Children and parents are informed of the result of the randomisation by the investigator.

After inclusion and randomisation, participants will be managed in 3 phases:

*period 1: *Full-time IP until somatic stabilisation (see below for definition); *period 2:* DP or IP according to their randomisation arm until weight normalisation is reached; *period 3:* OP follow-up.

*Period 1: *Full-time IP—identical for all included children- ongoing until somatic stabilisation, which is defined as: BMI over the 3^rd^ percentile, disappearance of somatic severity criteria for undernutrition such as bradycardia (heart rate below 40 per minute during sleep time or below 50 per minutes during day time), persistent disturbances of the biological balance (hypoglycaemia, hypophosphoremia, haemolysis, cytolytic hepatitis, elevated creatine kinase), or any somatic or biological manifestation requiring constant surveillance in hospital with usual medical, dietary and psychological care (persistent refusal to drink or eat, lipothemia, hypothermia). The treatment provides multi-disciplinary care for the child and his/her family as described in French guidelines [14], including:Child follow-up of AN and psychiatric comorbidities by a senior psychiatrist on a bi-weekly basisEndocrinologic and somatic evaluation by a senior endocrinologic paediatric for initial assessment M6 and M12 and by a psychiatrist resident for follow-up during IP and by a general practitioner during OPNutritional monitoring with a bi-weekly dietetic follow-upPsychological follow-up with weekly family therapyTherapeutic education for the child with a weekly psychoeducation group and day-care nurse follow-up

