#### Primary outcome

The primary non-inferiority outcome is BMI (Weight in kg/(Height in m^2^)) at 12 months after inclusion to assess non-inferiority on BMI maintenance.

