#### Secondary outcomes

*Biological and radiological outcomes* will be collected. *Nutritional status* will be assessed with prealbumin, leptin, total ghrelin and IGF1. Body composition and *bone mineralisation* will be estimated by using dual-energy X-ray absorptiometry (DEXA, GE Lunar ProdigyCorp., Madison. WI). Bone mineral measurements will be expressed as standard deviation score according to age and sex (SDS). *Bone maturation* will be assessed from an en face radiograph of the left wrist, interpreted using the Greulich and Pyle atlas.

*Global clinical and psychological evaluation* will be assessed with the *Clinical Global Impression* (CGI) [20] scale. CGI is scored on a two-part 7 response levels evaluating illness severity (CGI-S) and improvement (CGI-I) from 1 (“not ill”/ “very much improved”) to 7 (“extremely ill”/ “much worse”).

*Eating disorder symptomatology* will be assessed with the *Morgan and Russell scale* (MRS) [21] and the *Children Eating Disorders Inventory* (EDI-c) [22, 23]. The MRS is a questionnaire designed to evaluate the long-term evolution of the eating disorder and is used to assess the main aspects of anorexia nervosa over a six-month period. A version has been adapted for younger children, with deletion of non-appropriated items as "menstruation", "psychosexual functioning" and "emancipation". The assessment of the adapted procedure has 8 subscales divided into 3 groups: Eating; Mental status; Socioeconomic Status.

The EDI-c is adapted form of the EDI for children from 8 years of age onwards [22, 23]. This is a multidimensional self-questionnaire that assesses different psychological, behavioural and emotional characteristics associated with eating disorder symptoms. It comprises 91 items divided into 11 factors: Drive for Thinness, Bulimia, Body Dissatisfaction, Low Self-Esteem, Personal Alienation, Interpersonal Insecurity, Interpersonal Alienation, Interoceptive Deficits, Emotional Dysregulation, Perfectionism, Asceticism, and Maturity Fears. Each of the 91 items is rated from 'never' to 'always', respectively from 0 to 3 for direct items and from 3 to 0 for indirect items.

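### The unadjusted primary comparison of 12-month BMI is valid and meets its stated power, but it gives up precision that baseline data would supply at almost no cost

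*Protocol article*

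**What the plan says.** The Primary outcome section defines the endpoint on the raw scale: "BMI (Weight in kg/(Height in m^2^)) at 12 months after inclusion". The Statistical analysis plan section states that "the primary outcome for non-inferiority analysis is based on the comparison of the BMI at 1 year after inclusion between the two groups", using a two-sided 95% CI, and declares non-inferiority against a margin of 1 kg/m². One sentence then covers every endpoint: "The comparative analysis between the 2 groups for the primary or secondary criteria will be carried out using the appropriate tests". For continuous measures these are "Student's t test or non-parametric Wilcoxon test for quantitative variables". The only regression described there is a separate model with the MRS score as its dependent variable.

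The Sample size section uses the same one-sided t test, "assuming a distribution of the BMI of 16,6 ± 1,35" kg/m², and arrives at 40 per group, or 88 children after an allowance for dropout.

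Three further places bear on the point:
- Under Procedure, "Weight normalisation is individualised and will be determined at inclusion and before randomisation". The aim is to return each child to the earlier BMI trajectory, and two investigators do the calculation.
- Table 1 lists weight, height and BMI at inclusion. It does not list the target.
- Under Secondary outcomes, "Bone mineral measurements will be expressed as standard deviation score according to age and sex", so growth is allowed for there.

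**The concern.** Children are 8 to 13 years old at inclusion, and BMI varies with age and sex over that range. Both arms are treated until an individual target is reached, and that target is fixed before allocation. It is therefore a genuine baseline variable that describes where each child's BMI is meant to end up. Together with inclusion BMI, age and sex, it is a plausible predictor of 12-month BMI.

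A two-sample test leaves whatever these variables explain in the error term. The interval compared with the margin is then wider than it need be. A chance difference between the arms in age or target also stays in the estimate. In a single-centre trial of 88 children with a rare condition, precision that needs no further patients is worth having. This is a choice the article states, since it names the tests for the primary criterion, and not a gap left to a document that is not shown.

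**Working it through.** **Inputs.** From the Sample size section: margin 1 kg/m², SD 1.35 kg/m², one-sided alpha 0.025, 40 evaluable children per arm. Assumed because not stated: a true difference of 0, and R², the share of 12-month BMI variance explained by the baseline covariates.

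**Step 1: reproduce the plan's figure.**
- Standard error of the difference = 1.35 × √(2/40) = 0.302 kg/m².
- 95% CI half-width, 78 degrees of freedom = 1.991 × 0.302 = 0.60 kg/m².
- Noncentrality = 1/0.302 = 3.31, and the noncentral t distribution gives 90.5% power.
- With 39 per arm the power is 89.8%, so 40 is the smallest number that reaches 90%.

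The stated 40 per group reproduces, and it matches the stated unadjusted test.

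**Step 2: the same trial analysed by ANCOVA.** Take four covariates (inclusion BMI, age, sex, target BMI).
- Residual SD = 1.35 × √(1 − R²).
- Degrees of freedom = 80 − 2 − 4 = 74, critical value 1.993.
- Half-width = 1.993 × residual SD × √(2/40).
- Power from the noncentral t, with noncentrality 1/(residual SD × √(2/40)).

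| Assumed R² | Residual SD | 95% CI half-width (kg/m²) | Power |
|---|---|---|---|
| Unadjusted, as planned | 1.35 | 0.60 | 90.5% |
| 0 | 1.35 | 0.60 | 90.5% |
| 0.10 | 1.28 | 0.57 | 93.1% |
| 0.25 | 1.17 | 0.52 | 96.5% |
| 0.49 | 0.96 | 0.43 | 99.6% |

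If the covariates turn out useless, the four lost degrees of freedom make no visible difference. An R² of 0.10 to 0.49 corresponds to a multiple correlation of about 0.3 to 0.7.

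**Step 3: chance imbalance.** With 44 per arm, the difference between arms in a standardised baseline variable has a standard deviation of √(2/44) = 0.213. It lies within 1.96 × 0.213 = 0.42 SD in 95% of randomisations. At that limit, a covariate correlated ρ with the outcome moves the unadjusted difference by ρ × 1.35 × 0.42: about 0.17, 0.28 or 0.39 kg/m² for ρ of 0.3, 0.5 or 0.7. These are values at the edge of the 95% range and not typical ones. The unadjusted interval already allows for them. They show from another side the same variance that Step 2 removes, so they are not an additional loss.

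**The case against.** The strongest reply is that nothing here is wrong. The trial is sized with a t test and analysed with one, the two sections agree, and the stated power is met. That stands in full. A reader might infer that the unadjusted analysis is biased or underpowered, and the article supports neither. Randomisation balances the arms in expectation, and the confidence interval covers chance imbalance. Power falls below 90% only if the SD is larger than 1.35, and nothing in the article suggests that this figure leaves out the spread across ages 8 to 13.

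The gain is also unquantified in the article. All children enter severely undernourished, so inclusion BMI may have a restricted range and predict little. The target is a more plausible predictor, but no figure is given for it. This stands as well, which is why the range starts at zero.

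A reader might also conclude from the bone SDS that raw BMI is the wrong primary scale. That does not follow: a difference in mean BMI between randomised arms remains interpretable. ANCOVA keeps the raw scale, so it would not answer that complaint anyway. Moving to a standardised score would need a new margin and SD, which the article does not give.

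Finally, the article describes only a randomisation list. Silence on stratification in a condensed report carries no weight here. Nor does the absence of supportive or adjusted secondary analyses, which an analysis plan that is not shown may contain.

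What the reply does not remove is that the article names unadjusted tests for the primary criterion although suitable baseline variables exist.

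**Conclusion.** The point holds as a matter of efficiency, not as an error. The primary analysis is valid and reaches its stated power, but it forgoes precision and protection against chance imbalance. On the article's own inputs, adjustment would narrow the 95% CI half-width from 0.60 to between 0.57 and 0.43 kg/m² for an R² of 0.10 to 0.49, and raise power from 90.5% to between 93.1% and 99.6%. At an R² of 0 there is no gain and no material loss. The R² values and the zero true difference are assumptions; the SD, margin and numbers per arm are the article's. That no covariate is named for the primary test is certain. How much would be gained is not.

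**What to change.** Before the data are analysed, specify the primary analysis as an ANCOVA of 12-month BMI on arm, with inclusion BMI, age and sex as covariates. Add the pre-randomisation target, expressed as BMI (target weight over the square of inclusion height), provided one agreed value per child is recorded before randomisation. The article has two investigators calculate the target but does not say how differing values are resolved, and Table 1 does not list it as a recorded measure. If no single value was recorded, leave the target out.

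Judge the adjusted two-sided 95% CI against the unchanged 1 kg/m² margin. Keep the unadjusted t interval as a sensitivity analysis. An age- and sex-standardised BMI analysis may be added, as supportive only.

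The cost is wording in the protocol or analysis plan, three or four degrees of freedom, and a check that the target was stored. No additional children, visits or measurements are needed for inclusion BMI, age and sex.

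### The primary criterion sits inside a normality-dependent t/Wilcoxon choice, and the non-inferiority interval names no estimator, so the quantity compared with 1 kg/m2 is not fixed

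*Protocol article*

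**What the plan says.** All references are to the protocol article.

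- **Primary outcome section:** the outcome is BMI "at 12 months after inclusion to assess non-inferiority on BMI maintenance". It is a quantitative variable.
- **Sample size section:** the calculation uses Student's t test, one-sided at 2.5%, for 90% power. It is "based on the clinically determined non-inferiority margin for a difference in BMI of 1 kg/m2" and takes mean BMI as 16.6 with SD 1.35. This is a comparison of means.
- **Statistical analysis plan section, decision rule:** non-inferiority is concluded if the upper limit of the two-sided 95% interval for the between-group difference in BMI is below 1 kg/m2. The text does not say whether this is a difference in means or another location measure.
- **Same section, next sentence:** "The comparative analysis between the 2 groups for the primary or secondary criteria will be carried out using the appropriate tests". For quantitative variables these are Student's t or the "non-parametric Wilcoxon test for quantitative variables, according to their normal or non-normal distribution".
- **Same section, descriptive analysis:** summaries also switch, from mean (SD) to median [IQR], when a variable is not normal.

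No criterion for normality is given, and nothing says what happens to the primary interval if the Wilcoxon branch is taken.

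**The concern.** A non-inferiority conclusion needs one target quantity, fixed in advance and measured on the scale of the margin. Here the margin and sample size are on the mean scale, but the sentence on tests lets the distribution of the outcome data choose the method for the primary criterion.

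The ordinary Wilcoxon test has equality of the two distributions as its null hypothesis. It contains no margin, so its p-value cannot show non-inferiority at 1 kg/m2. Its companion Hodges-Lehmann interval can be set against 1 kg/m2, but it estimates the median of all pairwise between-group differences. That equals the mean difference under a pure location shift, and in general not otherwise. If a minority of children in the experimental arm did badly, the mean deficit would exceed the Hodges-Lehmann shift, and the same low tail would make the normality check more likely to fail. The trial's confirmatory conclusion could then rest on a quantity that understates the mean deficit.

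**Working it through.** **Step 1. Reproduce the sample size on the mean scale.** Inputs from the Sample size section: margin 1 kg/m2, SD 1.35, one-sided alpha 0.025, power 0.90. The true difference is taken as 0, which is implied.

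- Normal approximation: n per arm = 2 × (1.960 + 1.282)² × 1.35² / 1² = 38.3, rounded up to 39.
- Exact non-central t: power is 89.8% at 39 per arm. At 40 per arm the non-centrality is 1 / (1.35 × √(2/40)) = 3.31 on 78 degrees of freedom, and power is 90.5%.

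The stated 40 per arm is therefore right for a t-based comparison of means.

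**Step 2. Simulate the possible readings of the interval.** There were 40 children per arm and 4000 simulated trials per scenario. The control arm is N(16.6, 1.35). In the mixture scenarios a fraction p of the experimental arm is lowered by d kg/m2, so the true mean deficit is p × d. The difference is taken as control minus experimental, the direction in which an upper limit below 1 makes sense. Three rules were compared:

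- *Mean interval:* (mean of control − mean of experimental) + t(0.975; 78) × √((s_c² + s_e²)/40) < 1.
- *Rank interval:* Wilcoxon test after shifting by 1 kg/m2, one-sided 0.025 (equivalent to a Hodges-Lehmann interval).
- *Switch:* rank interval if Shapiro-Wilk rejects at 5% in either arm, otherwise mean interval. The 5% criterion is an assumption, since the article gives none.

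False non-inferiority at a true mean deficit of about 1.0 (nominal 2.5%):

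| Experimental arm | Mean deficit | Hodges-Lehmann shift | Normality rejected | Mean interval | Rank interval | Switch |
|---|---|---|---|---|---|---|
| Pure normal shift | 1.0 | 1.0 | 10.0% | 2.7% | 2.8% | 2.9% |
| 40% lower by 2.5 | 0.40 × 2.5 = 1.0 | 0.96 | 10.7% | 2.2% | 3.0% | 2.3% |
| 33% lower by 3 | 0.33 × 3 = 0.99 | 0.89 | 15.9% | 2.8% | 4.4% | 3.3% |
| 25% lower by 4 | 0.25 × 4 = 1.0 | 0.74 | 48.6% | 3.8% | 9.5% | 8.2% |
| 20% lower by 5 | 0.20 × 5 = 1.0 | 0.60 | 85.0% | 3.1% | 17.5% | 16.7% |

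A repeat simulation at SD 1.35 gave, for the switch, 2.9%, 2.5%, 3.5%, 8.0% and 15.8% in the same row order (with one third in place of 33%). The mean interval ranged from 2.2% to 3.7%. The two sets agree to within about 1 percentage point.

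**Step 3. See whether the switch buys anything.** With normal data and no true difference, power was 90.6% for the mean interval, 89.3% for the rank interval and 90.5% for the switch. Under the design assumptions the switch gains nothing.

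**The case against.** The strongest reply is that the decision rule is already fixed. It stands immediately before the sentence on tests, it is expressed as an interval against 1 kg/m2, and the trial is sized on a t test. On that reading the sentence on tests is a general catalogue and its p-value merely accompanies the interval. This stands in part: nothing in the article says that a Wilcoxon result replaces the interval rule. It does not settle the matter, because the sentence names the primary criterion, the interval names no estimator, and the descriptive summaries in the same section do switch with normality.

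A reader might infer that the plan would take a non-significant Wilcoxon test as evidence of non-inferiority, and might then count how often that test misses a deficit of 1.0 kg/m2. The article contains no such rule. Such a count reflects mainly the type II error of any difference test, the ordinary t test included, so it is no measure of harm here.

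A reader might also infer that a low-BMI tail confined to the experimental arm is the expected result. The article does not support that. Its Procedure section provides for readmission of day-patient children who deteriorate, and for the same outpatient follow-up of all children after weight normalisation. It thus recognises that some may do badly, but it gives no 12-month distribution beyond 16.6 ± 1.35.

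**Conclusion.** The point holds as a conflict between two adjacent sentences about the primary analysis: a margin rule with an unnamed estimator, and a data-dependent choice of test that expressly includes the primary criterion. It is not a stated replacement of the decision rule.

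The size depends on two things that the article does not settle. If the interval is always for the mean difference, there is no inflation from the switch, and error stays at about 2-4%. If the interval follows the switch, false non-inferiority at a true mean deficit of 1.0 kg/m2 runs from about 2.5-3% (pure shift or widely spread deficit) to about 8-16% (20-25% of the experimental arm 4-5 kg/m2 lower). The upper figures rest on assumed mixtures, SD 1.35, 40 evaluable children per arm and a 5% Shapiro-Wilk criterion. They show what could happen and are not a forecast.

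**What to change.** State, before outcome data are seen, that the primary analysis is always the two-sided 95% confidence interval for the difference in mean 12-month BMI (t-based, direction of subtraction given), compared with 1 kg/m2 whatever the distribution. Name a bootstrap or robust-standard-error interval for the same mean difference as a sensitivity analysis. Remove the primary criterion from the t/Wilcoxon sentence, and label any rank-based analysis of BMI as supportive only.

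The cost is a sentence or two of text. The required 80 evaluable and 88 recruited children do not change, and power stays at 90.5% with 40 per arm.

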Demonstrate non-inferiority of a stepped-care model of DP after short IP stabilisation versus full-time IP based on BMI at 12 months post-randomisation (primary outcome).Demonstrate non-inferiority of a stepped-care model of DP after short IP stabilisation in term of clinical, biological outcomes, AN symptoms, comorbidities, and relapse at different time points (weight normalization, 6, 12 months).Assess the impact of a stepped-care model of DP after short IP stabilisation versus full-time IP on treatment satisfaction and quality of life of patients and parents at 6 and 12 months.Assess the impact of the prospect of discharge to DP on initial IP (duration before somatic stabilisation, motivation to change) at inclusion and somatic stabilisation.Determine factors associated with positive response to stepped-care model of DP after short IP.Determine the cost-utility and cost-effectiveness of a stepped-care model of DP after short IP stabilisation compared with full-time IP.

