### Measures (Table 1)

**Table 1 Tab1:** Overview of measures and time of assessment

Assessment	Inclusion	Stabilisation	Weight normalization	6 months	12 months
*Clinical assessment weight, height, BMI *	x	x	x	x	x
tanner stage	x			x	x
*Nutritional markers* prealbumin, leptin, total ghrelin and IGF1	x		x		x
*Radiology* Bone mineralization (dual-energy X-ray absorptiometry) Bone maturation (en face radiograph of the left wrist)	x				x
*Global psychosocial* CGI	x		x	x	x
*Eating symptomatology* EDI-c, MRS	x		x	x	x
*Anxiety and depressive symptomatology* CDI, STAIC	x		x	x	x
*Self-esteem Scale* Rosenberg	x		x	x	x
*Motivation to change* HAQ-11S, Motivation questionnaire	x		x	x	x
*Treatment acceptability and quality of life* CSQ-8, SF-12	x		x	x	x
Resource consumption		x	x	x	x

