*Depressive and anxiety symptomatology* will be respectively assessed by the Children Depression Inventory (CDI) [24], the *State –Trait Anxiety Inventory for Children* (STAIC) [25]. The CDI is a self-adapted Beck Depression Inventory for children aged 7 to 17 years, with 27 items scored from 0 (absent or normal behaviour for age) to 2 (severe). The total score, calculated as the sum of all the items, varies from 0 to 54 with a pathological threshold of 15. It is a widely used tool in the international literature to assess the intensity of depression.

The STAIC is a self-questionnaire and comprises two 20-item subscales, the Trait Anxiety and the State Anxiety. The scores observed for the two subscales range from 20 to 80, with a score of 35 or less corresponding to very low anxiety and a score of over 65 corresponding to very high anxiety.

*Self-esteem will be assess by the Rosenberg Self-esteem Scale * [26]* is* a self-questionnaire with a 10-items measure of global self-esteem, widely used in general and clinical populations. The higher the scores, the better the self-esteem. It can be used from the age of 8 years.

*Therapeutic alliance/perception of treatment benefit and Motivation to change* will be assessed by the *Helping Alliance Questionnaire-11* (HAQ-11S) [27], the *Consumer Satisfaction Questionnaire* (CSQ-8) [27] and the *Motivation Questionnaire* [28].

The CSQ-8 is a self -"satisfaction"-questionnaire, defined here as a concept tending to assess whether the needs of the consumer of a service are being met or not. In medical terms, patient satisfaction is an internationally recognized measure for the evaluation of the perception of quality of care; this dimension can have an influence on the outcome and adherence to the proposed treatment and thus on the acceptability of the treatment. It consists of eight questions, each with four response options ranging from one "not at all satisfied" to four "completely satisfied".

The HAQ-11S is a self-questionnaire of 11 items measuring the strength of the collaboration between the patient and the healthcare team.

The Motivation Questionnaire will assess the importance of change and the perceived ability to change. It consists of two questions: "How important is it for you to change" and "How confident are you in your ability to change". Both questions are rated on a Likert scale from 0: "Not at all" to 10: "Completely".

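### As listed, the regression for factors associated with the effect of the intervention has no arm term and no arm-by-factor interaction, so it can identify only prognostic factors.

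*Protocol article*

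**What the plan says.** The fifth specific objective (protocol article, Background) is: "Determine factors associated with positive response to stepped-care model of DP after short IP". The Statistical analysis plan section turns this into an analysis. It speaks first of prognosis factors and then says that "a regression model will be used to search for factors associated with the effect of the intervention, integrating the MRS score" as the outcome. The explanatory variables are "the CGI score, the HAQ11 and motivation questionnaire scores, and the severity of the weight deficit as explanatory variables". The sentence names no treatment arm, no interaction and no restriction to one arm.

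The Sample size section gives 80 evaluable children (40 per group) and 88 randomised (44 per group). No figure is given for this regression.

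**The concern.** In a two-arm trial the effect of the intervention is a contrast between arms. A factor is associated with that effect only if the contrast changes with the factor, and only an arm-by-factor term can show this. The listed terms contain nothing from which the contrast could be estimated. Followed as written, the analysis would answer a different question from the one the article states. A factor that predicts a worse MRS equally in both arms could be reported as bearing on the effect of stepped care. A factor that truly changes the comparison could be missed.

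**Working it through.** **Inputs.** From the article: MRS as outcome, the four listed factors, 1:1 allocation, 40 evaluable per arm. Assumed, because the article gives no such figures: correlation r between a factor and MRS of 0.3, 0.4 or 0.5; independent standard-normal factors; standardised outcome; two-sided 5% tests.

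**The plan's own figure.** With margin 1, SD 1.35, one-sided 2.5% and 90% power, the normal formula gives 2 × 1.35² × (1.960 + 1.282)² / 1² = 38.3, so 39 per arm. The exact t calculation gives power 0.898 at 39 and 0.905 at 40, so 40 per arm and 80 in total. Then 80 × 1.10 = 88. The stated sample size reproduces and is not at issue.

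**What each model estimates.** Let A be the arm (1 = stepped care) and x a factor measured before allocation. Write the true mean of MRS as b0 + bA·A + bx·x + bAx·A·x.

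- The effect of the intervention at x is bA + bAx·x. A factor associated with that effect is one with bAx ≠ 0.
- Listed model, both arms, 1:1: the slope on x is the average of the two arm slopes, bx + bAx/2. It can be large when bAx = 0, and zero when bAx is not.
- Listed model, stepped-care arm only: the slope is bx + bAx. Without the control arm the two parts cannot be separated.
- Model with A and A·x: bAx is estimated directly.

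**How often a purely prognostic factor (bAx = 0) is flagged.** Simulation, 5,000 runs per setting, four factors in the model:

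| r | Listed model, N=80 | Stepped-care arm only, n=40 | Interaction test, N=80 |
|---|---|---|---|
| 0.3 | 77% | 45% | 5.2% |
| 0.4 | 96% | 70% | 5.1% |
| 0.5 | 99.8% | 90% | 4.6% |

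With 88 children the listed model gives 80%, 97% and 99.8%.

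Hand check for one factor at r = 0.4 with Fisher's z, power = Φ(atanh(r)·√(n − 3) − 1.96), where atanh(0.4) = 0.4236:

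- n = 80: 0.4236 × √77 − 1.96 = 1.757, power 0.96.
- n = 40: 0.4236 × √37 − 1.96 = 0.617, power 0.73. The simulation gives 70% because four factors are fitted together.

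**The reverse case.** For a pure modifier with slopes +r in one arm and −r in the other, the average slope is zero. The listed model flags it in only 6% to 8% of runs at N=80, close to chance.

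**What an interaction test can detect.** With factor and residual SD taken as 1, the standard error of the slope difference is √(2/40) = 0.224. The difference detectable with 80% power is 2.80 × 0.224 = 0.63 SD of MRS per SD of the factor (0.60 at N=88). At N=80 power is Φ(0.5/0.224 − 1.96) = 61% for a difference of 0.5 and 27% for 0.3. The 5% error rate is per factor: four independent tests give 1 − 0.95⁴ = 19% for at least one false flag.

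**The case against.** The best defence is that both the objective and the opening of the analysis sentence can be read as asking for prognosis among children given stepped care. For that question a main-effects model in that arm is an ordinary choice, and only the clause about the effect of the intervention is out of place. This reading is coherent. It narrows the defect to a contradiction between the stated aim and the listed terms, but does not remove it: a fit in one arm still says nothing about the effect relative to inpatient care.

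A second defence is that one sentence in an article is not a full model specification, and an SAP that is not shown could add the arm and interaction terms. That is possible, so the point is about the model as listed and does not predict what will be reported. But the article did not leave the model open. It named the outcome and the explanatory variables, and those do not serve the aim given in the same sentence.

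Third, the high percentages are power to detect a real prognostic association. They are error rates only if the result is read as effect modification. That is correct, and it is the reading the article's wording invites.

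Two stronger inferences should not be drawn:

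- A reader might infer from the Measures table, which schedules "HAQ-11S, Motivation questionnaire" and CGI after randomisation as well as at inclusion, that follow-up scores will be used to explain follow-up MRS, which would be circular. The article does not say so. Inclusion values exist, and the choice of visit is detail that an SAP commonly settles.
- A reader might infer that the results would be used to withhold day care from some children. The article says only that factors will be determined and states no such use.

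**Conclusion.** The point holds for the model as listed. Without an arm term and an arm-by-factor term it cannot identify factors associated with the effect of the intervention; it identifies prognostic factors, pooled or within stepped care. Across assumed correlations of 0.3 to 0.5, a factor with no modifying effect would be flagged in about 77% to 99.8% of trials at N=80, or 45% to 90% in the stepped-care arm alone, against about 5% per factor with an interaction test. The sizes rest on the assumed correlations, independent factors and a standardised outcome. The mismatch itself follows from the model terms and needs none of these. It concerns one secondary objective of an exploratory kind and leaves the primary non-inferiority conclusion untouched.

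**What to change.** Choose the question and make the text match it.

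- **If effect modification is meant:** fit both arms together, with MRS on arm, each factor at its inclusion value, and arm-by-factor terms. Report each interaction with its 95% confidence interval, label the analysis exploratory, and state how many factors are tested.
- **If prognosis within stepped care is meant:** say that the model is fitted in that arm and estimates prognostic factors, and remove the claim about the effect of the intervention.

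Either change is one of wording and uses scores already scheduled at inclusion; no visit, measure or child is added. The cost of the first option is imprecision: only large slope differences (about 0.63 SD per SD at N=80) are detectable with 80% power, and with several factors tested an isolated significant interaction should be read with caution.
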